**Secondary outcomes — Postoperative complications**			
Postoperative complications	All complications occurring through postoperative day 30, classified using the Clavien–Dindo classification; reported by grade and as the proportion at grade ≥II	Through POD 30	Chi-square or Fisher’s exact test
Specific complications	Surgical site infection; pneumonia; delayed gastric emptying; anastomotic leak	Through POD 30	Chi-square or Fisher’s exact test
**Secondary outcomes — Functional recovery**			
Time to first flatus/ defecation	First documented passage of flatus and stool	POD 1–14	Log-rank test; Kaplan–Meier estimates
Time to tolerate ≥50% of soft diet for 24 h	First day of meeting the threshold sustained for 24 h	POD 2–5	Log-rank test; Kaplan–Meier estimates
Time to independent corridor ambulation	First documented day of independent corridor walking	POD 1–5	Log-rank test; Kaplan–Meier estimates
Length of postoperative hospital stay	Days from surgery to discharge	Through discharge	Two-sample t-test or Wilcoxon rank-sum test
Patient-reported recovery (oral intake, GI symptoms, ONS use, activity)	Meal frequency, early satiety, appetite loss, nausea/vomiting, dumping, reflux, diarrhoea, constipation; oral nutritional supplement use; physical activity (≥30 min, ≥ 3 × /week)	POD 14, 1, 3, 6, 12 months	Two-sample t-test or Wilcoxon rank-sum (continuous); Chi-square or Fisher’s exact (categorical)
Clinical events	Emergency department visits, readmissions, interventions	Through 12 months	Chi-square or Fisher’s exact test; incidence rate ratio
**Safety outcomes**			
Adverse events, adverse drug reactions, and serious adverse events	Any adverse event, adverse drug reaction (per investigator’s causality assessment), or serious adverse event recorded throughout the intervention and follow-up period	Through 12 months	Descriptive (number of participants, events, incidence proportion); Chi-square or Fisher’s exact test for between-group comparison
Laboratory safety	Aspartate and alanine aminotransferase, blood urea nitrogen, serum creatinine, glucose, electrolytes	POD −1, POD 3, POD 5, 1, 3, 6, 12 months	Descriptive summary; between-group comparison at each timepoint

All analyses will be performed on the intention-to-treat population, with per-protocol analysis as a sensitivity analysis. Two-sided α = 0.05 will be used throughout. The single primary endpoint is the sole confirmatory analysis. The two key secondary endpoints — POD 3 nitrogen balance (reported with the nitrogen balance trajectory) and the early change in serum prealbumin, defined as the change from the preoperative (POD −1) baseline to POD 5 — are controlled for family-wise error at 0.05 by the Holm procedure, independently of the primary result; all other secondary outcomes are exploratory and reported with 95% confidence intervals without multiplicity adjustment. For the primary endpoint, genuine missing data are handled by multiple imputation under the missing-at-random assumption as the primary approach, with complete-case analysis as a sensitivity analysis and a delta-adjusted (tipping-point) analysis under missing-not-at-random assumptions. Full specifications are given in the dated statistical analysis plan (SAP v1.0, 21 July 2026). Abbreviations: APCT, abdominopelvic computed tomography; CAR, C-reactive protein–to-albumin ratio; GLIM, Global Leadership Initiative on Malnutrition; mGPS, modified Glasgow Prognostic Score; NRS-2002, Nutritional Risk Screening 2002; ONS, oral nutritional supplement; PNI, Prognostic Nutritional Index; POD, postoperative day.

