### Eligibility criteria

Adults aged 19 years or older who are scheduled to undergo curative gastric cancer surgery and provide written informed consent are eligible. Detailed inclusion, exclusion and withdrawal criteria are presented in Table 1. Eligibility is based on the planned extent of resection: planned total and distal (subtotal) gastrectomy are eligible, whereas planned proximal gastrectomy is excluded; all standard reconstructions (Billroth I, Billroth II, Roux-en-Y) and surgical approaches (open, laparoscopic, robotic) are permitted. If the actual procedure differs from the plan (including an unplanned proximal gastrectomy), the participant is retained and analyzed in the allocated arm under the intention-to-treat principle, with the actual procedure recorded and examined in per-protocol and sensitivity analyses. Patients with clinically significant hepatic or renal impairment are excluded by the screening laboratory thresholds listed in Table 1, and hepatic and renal function are monitored daily during the intervention.

**Table 1 pone.0355677.t001:** Inclusion and exclusion criteria.

Inclusion criteria	Exclusion criteria
1. Adults ≥19 years of age scheduled to undergo curative gastric cancer surgery	1. Uncontrolled severe comorbidity, including: • Decompensated diabetes mellitus • Cerebrovascular or major cardiovascular event (acute myocardial infarction, stroke, pulmonary embolism) within the prior 6 months • Sepsis • Heart failure
2. Able and willing to provide written informed consent	2. Receipt of parenteral nutrition within 7 days prior to randomisation
	3. Severe preoperative metabolic abnormality on screening laboratory tests, defined as any of: • Triglyceride > 400 mg/dL • AST or ALT > 3 × upper limit of normal (ULN) • Total bilirubin > 3 × ULN • Serum creatinine > 2 × ULN • HbA1c > 9.0% • Potassium < 3.0 or > 6.0 mEq/L • Calcium > 12.5 mg/dL • Sodium > 155 mmol/L • Magnesium > 3.0 mg/dL
	4. Any other condition that, in the investigator’s judgment, makes the participant unsuitable for the trial 5. Planned proximal gastrectomy

Withdrawal criteria: participants who develop severe intra- or postoperative complications (e.g., massive hemorrhage requiring re-operation) or severe infusion-related events that preclude further peripheral parenteral nutrition (e.g., refractory infusion-site pain or phlebitis) will be withdrawn from the per-protocol analysis but retained in the intention-to-treat population.

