**Caloric target and dose calculation.** The daily caloric target during the intervention period is set at 20 kcal/kg/day, in keeping with current evidence supporting permissive hypocaloric feeding to avoid perioperative overfeeding. Body weight used for dose calculation is determined by body mass index (BMI): actual body weight is used for participants with BMI < 25 kg/m², and ideal body weight—calculated as height (m)² × 23 (a reference body-mass index of 23 kg/m², consistent with recommendations for Asian populations) [21], applied to both sexes—is used for those with BMI ≥ 25 kg/m². The required daily PN volume is back-calculated from the caloric target using the energy density of the assigned product (0.69 kcal/mL for the control and 0.67 kcal/mL for the investigational product), rounded to the nearest 1 mL, and delivered through a volumetric infusion pump. The calculated daily volume is not expected to exceed the manufacturer-stated maximum of 40 mL/kg/day. For a 75-kg participant, the control formulation delivers approximately 68 g of amino acid per day (0.9 g/kg) and the high-protein formulation approximately 84 g (1.1 g/kg); detailed examples are provided in S2 and S3 Tables. These amino-acid amounts represent PN-only delivery; the total protein supply (oral plus parenteral) that forms the basis of the nitrogen-balance calculation is higher, and the between-arm difference should be interpreted as a difference in PN-delivered rather than total protein.

**Stepwise PN delivery schedule.** PN is administered through a peripheral intravenous line; central venous access is not required. Peripheral access was chosen to avoid the infection and thrombosis risks of central venous catheterisation, consistent with the broader Enhanced Recovery After Surgery (ERAS) principle of minimizing invasive perioperative procedures. PN is initiated on the preoperative day (preoperative day −1; POD −1), withheld on the day of surgery (POD 0) because of perioperative anaesthetic and surgical considerations, and resumed from POD 1 through POD 5, for a total of six administration days. The PN dose on each day is delivered as a fixed proportion of the daily caloric target, decreasing stepwise as anticipated oral intake advances: 80% on POD −1, 100% on POD 1, 60% on POD 2 and POD 3, and 50% on POD 4 and POD 5. The stepwise schedule is summarized in Table 3.

**Table 3 pone.0355677.t003:** Stepwise perioperative parenteral nutrition delivery schedule.

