Postoperative day	Oral diet stage	Anticipated mean oral energy intake (kcal/day)*	Scheduled PN coverage (% of daily caloric target)
POD −1	Preoperative oral carbohydrate loading	≈200 (per protocol)	80%
POD 0	Surgery — nil per os	—	PN withheld
POD 1	Sips of water	—	100%
POD 2	Post-gastrectomy liquid diet	≈350	60%
POD 3	Post-gastrectomy early soft diet	≈315	60%
POD 4–5	Post-gastrectomy soft diet	≈820	50%

PN, parenteral nutrition; POD, postoperative day. *Anticipated oral energy intake for POD 2 through POD 5 is derived from a 1-year retrospective audit of post-gastrectomy hospital meal intake at the participating institution (August 2024 – July 2025; n = 92, 160, and 102 measurements for the liquid, early soft, and soft diet stages, respectively); detailed values are provided in S1 Table. The daily caloric target is set at 20 kcal/kg/day, calculated using actual body weight when BMI < 25 kg/m² and ideal body weight (height [m]² × 23) when BMI ≥ 25 kg/m². The corresponding daily PN volume is back-calculated from the assigned product’s energy density (0.69 kcal/mL for the control and 0.67 kcal/mL for the investigational product), rounded to the nearest 1 mL, and delivered through a volumetric infusion pump. Preoperative oral carbohydrate loading is provided in two 200-mL servings on POD −1 of a commercially available carbohydrate-rich nutritional supplement (Nucare NoenPiO; Daesang Wellife, Republic of Korea), to maintain preoperative carbohydrate intake before the institutional mandatory fasting period (initiated from the evening of POD −1 owing to indocyanine green injection for sentinel lymph node mapping), in keeping with the underlying Enhanced Recovery After Surgery Society principle of avoiding prolonged preoperative fasting.

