**Monitoring and dose modification.** During the intervention period, blood glucose, serum electrolytes, hepatic and renal function tests, body weight, and urine output are monitored daily by the NST. The assigned PN may be temporarily withheld or reduced at the investigator’s discretion for predefined safety triggers, including blood glucose ≥250 mg/dL, clinically significant hepatic enzyme elevation, or mild to moderate infusion-site reactions. Permanent discontinuation of the allocated PN with withdrawal from the per-protocol population is reserved for severe intra- or postoperative complications — including anastomotic leak, bacteremia, or fungemia — and for severe infusion-related events that preclude further PN (e.g., refractory infusion-site pain or phlebitis); in such cases the allocated PN is discontinued at the discretion of the treating clinician, and the participant is retained in the intention-to-treat population and flagged for sensitivity analysis. Any modification or discontinuation of the assigned regimen, together with the reason, is documented on the case report form. Adherence to the allocated intervention is summarized as the proportion of planned PN doses received and the cumulative volume of allocated PN administered during POD −1 through POD 5.

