**Fig 2 pone.0355677.g002:**
[figure not shown]
PROGAIN trial flow from recruitment through follow-up. Schematic overview of the trial conduct. Eligible patients are screened, randomized 1:1 to amino acid–enriched (high-protein) peripheral PN or conventional peripheral PN in an open-label, parallel-group design, and receive the assigned PN from preoperative day −1 through postoperative day (POD) 5 alongside standardized perioperative diet advancement. Daily intervention-period assessments include meal intake logs, with blood glucose monitoring on POD 5 and skeletal muscle index assessed from baseline and follow-up computed tomography, and laboratory and functional recovery measures. Outpatient follow-up visits at POD 14 and at 1, 3, 6, and 12 months capture body weight, nutritional indices, mGPS, CAR/PNI, and clinical events. The primary outcome is nitrogen balance on POD 5; secondary outcomes include nutritional, glycemic, complication, and functional recovery measures. CAR, C-reactive protein–to-albumin ratio; mGPS, modified Glasgow Prognostic Score; PN, parenteral nutrition; PNI, Prognostic Nutritional Index; POD, postoperative day.

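### The in-hospital laboratory safety comparison uses only POD −1, POD 3 and POD 5, leaving out the daily POD 1, 2 and 4 results and any abnormal value on those days that led to a PN hold

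*Protocol article*

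**What the plan says.** In Table 4 of the protocol article (Safety outcomes, Laboratory safety) the analytes are "Aspartate and alanine aminotransferase, blood urea nitrogen, serum creatinine, glucose, electrolytes". The timepoints are "POD −1, POD 3, POD 5, 1, 3, 6, 12 months" and the analysis is "Descriptive summary; between-group comparison at each timepoint".

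Monitoring is denser than that. Under Interventions, the paragraph on monitoring and dose modification states that "blood glucose, serum electrolytes, hepatic and renal function tests, body weight, and urine output are monitored daily by the NST". Eligibility criteria repeats that "hepatic and renal function are monitored daily during the intervention". The same Interventions paragraph lets the investigator withhold or reduce PN for predefined triggers. Those it names are glucose of 250 mg/dL or more, clinically significant hepatic enzyme elevation, and mild to moderate infusion-site reactions. Every modification and its reason goes on the case report form.

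The PN schedule is "80% on POD −1, 100% on POD 1, 60% on POD 2 and POD 3, and 50% on POD 4 and POD 5" of the daily caloric target, with none on the day of surgery.

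The Fig 2 caption describes the in-hospital assessments "with blood glucose monitoring on POD 5 and skeletal muscle index assessed from baseline and follow-up computed tomography". The glycaemic outcomes in Table 4 cover POD 0–5: any glucose of 180 mg/dL or more, and total insulin.

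**The concern.** The results for POD 1, 2 and 4 should exist, because the protocol requires daily tests, but the planned laboratory comparison does not use them. Two things follow.

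First, the day with the largest same-day difference in delivered product, POD 1, is not compared, and neither is POD 2, the day after it.

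Second, the omission can be selective. An abnormal value on POD 1, 2 or 4 may cause PN to be withheld or reduced. The next value in the table, on POD 3 or POD 5, is then taken after that response. The value that prompted the action is absent and a possibly recovered one stands in for it. If holds were more frequent in one arm, the fixed-day comparison would lean towards no difference.

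This matters because laboratory assays are run without knowledge of allocation, whereas the nutrition support team and bedside investigators know the arm. Table 4 lists no other between-arm comparison of aminotransferase, urea, creatinine or electrolyte values. There is also no data and safety monitoring board.

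**Working it through.** **Inputs.** Target 20 kcal/kg/day; energy density 0.69 (control) and 0.67 kcal/mL (investigational); amino acids 31.5 and 37.4 mg/mL; nitrogen 5.21 and 6.17 mg/mL; potassium 18.9 and 22.5 mmol/L (Table 2 and the dose-calculation paragraph). Coverage is from Table 3. Body weight is an assumption where used: 60 kg, with 70 kg as a second value.

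**Formula.** Volume = 20 × weight × coverage ÷ energy density. Delivered amount = volume × content per mL.

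**Reproducing the plan's own figure.** The Sample size section gives a between-arm nitrogen difference of about 1.0–1.2 g on POD 5 and roughly 8 g over six days.
- 60 kg, full coverage: volumes 1200/0.69 = 1739 mL and 1200/0.67 = 1791 mL; nitrogen 9.06 and 11.05 g; difference 1.99 g.
- POD 5 at 50%: 0.99 g at 60 kg, 1.16 g at 70 kg.
- Coverages sum to 0.8 + 1.0 + 0.6 + 0.6 + 0.5 + 0.5 = 4.0, so the cumulative difference is 1.99 × 4.0 = 7.96 g at 60 kg (9.29 g at 70 kg).

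The stated figures reproduce at about 60–70 kg for POD 5 and about 60 kg for the total.

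**Same-day contrast.** Amino acids at full coverage: 20/0.67 × 37.4 = 1116 mg/kg and 20/0.69 × 31.5 = 913 mg/kg, a difference of 0.203 g/kg.

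| Day | Coverage | Amino-acid difference (g/kg) | Nitrogen difference at 60 kg (g) | Potassium difference at 60 kg (mmol) | In laboratory comparison |
|---|---|---|---|---|---|
| POD 1 | 100% | 0.203 | 1.99 | 7.4 | no |
| POD 2 | 60% | 0.122 | 1.19 | 4.5 | no |
| POD 3 | 60% | 0.122 | 1.19 | 4.5 | yes |
| POD 4 | 50% | 0.102 | 0.99 | 3.7 | no |
| POD 5 | 50% | 0.102 | 0.99 | 3.7 | yes |

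The POD 1 contrast is 1/0.6 = 1.67 times that of POD 3 and 1/0.5 = 2.0 times that of POD 5, at any weight. POD −1 is also in the row, at 80% coverage, but Table 4 uses that day as the preoperative baseline for prealbumin.

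**Cumulative contrast.** Summed coverage from POD −1 is 180% after POD 1, 300% after POD 3 and 400% after POD 5. The amino-acid difference accumulates to 0.203 × 1.8 = 0.37, 0.203 × 3.0 = 0.61 and 0.203 × 4.0 = 0.81 g/kg. By this measure POD 5 carries the most, not the least.

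**What is covered elsewhere.** Any glucose at the 250 mg/dL trigger is also at or above 180 mg/dL, so it counts in the POD 0–5 hyperglycaemia outcome. That outcome does not distinguish a value just over 180 from one at the trigger. For the other analytes, Table 4 has no corresponding any-day outcome.

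**The case against.** The strongest reply has four parts.

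1. Glucose is already compared over the whole period, with adjustment for diabetes, together with insulin use. This stands. A reader might infer that a glucose difference on POD 1 would go unseen; the documents do not support that. Only the trigger-level comparison is missing.

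2. Other abnormalities have a second route: adverse events are identified partly through laboratory monitoring and are compared between arms, and holds are recorded with reasons. This stands in part. That route depends on judgement by staff who know the allocation, and it does not compare the values themselves.

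3. Same-day dose is not laboratory effect. This stands. A reader might take 60% and 50% as the share of signal retained on POD 3 and POD 5. But the cumulative contrast is largest on POD 5, draw times are not given, and a POD 1 sample might precede most of that day's infusion.

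4. Table 4 sets outcome timepoints while the Interventions section governs monitoring, so the two do not conflict. This stands. It might be inferred that staff following Table 4 or Fig 2 could not apply the triggers on POD 1, 2 or 4; in a single-centre trial with daily monitoring stated twice, that is speculation. The Fig 2 sentence itself places laboratory measures among the daily assessments, so only its wording on glucose needs attention.

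It may also be said that worst-value tables belong in the statistical analysis plan, which is not shown. But Table 4 does not leave the timepoints open; it states them, and the article says that Table 4 gives the timepoints and prespecified analyses.

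**Conclusion.** The point holds as a modest weakness in safety reporting. For aminotransferases, urea, creatinine and electrolytes, the stated comparison uses two of five postoperative PN days, omits the one full-coverage day, and can replace an abnormal value by a later one taken after a hold. How much this would hide cannot be computed: the documents give no hold rate, no draw times and no laboratory variability. Of the laboratory triggers the article names, only hepatic enzyme elevation concerns these analytes, although its list is introduced as inclusive rather than complete.

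It would go too far to say that the safety conclusion rests on this row. Adverse events, graded infusion-site reactions, Clavien–Dindo complications and the glycaemic outcomes also contribute. The conclusion assumes that the daily tests are done and retrievable as the protocol states. No sample size, power or alpha figure changes.

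**What to change.** Keep the POD 3 and POD 5 comparisons. Add to the laboratory safety row a descriptive by-arm comparison over POD 1–5, from results already measured daily, of:
- the worst value of each analyte, with its direction stated in advance for electrolytes;
- the proportion of participants crossing each existing laboratory trigger for withholding or reducing PN. The article gives a number only for glucose, so the hepatic trigger can be counted from the holds and reasons on the case report form.

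Reconcile the Fig 2 caption on glucose with the daily monitoring under Interventions and with the POD 0–5 glycaemic outcomes. If the statistical analysis plan already contains such a summary, Table 4 need only be aligned with it.

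The cost is extra data entry from the medical record and one more exploratory safety table. No sampling is added and no clinical rule changes. It should be settled before the coded labels are unmasked.

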**Secondary outcomes, subgroups, and missing data.** The single primary endpoint is the sole confirmatory analysis (two-sided α = 0.05). Two key secondary endpoints — POD 3 nitrogen balance and early change in prealbumin, both objective, blinded, and responsive to short-term protein delivery — are controlled for family-wise error at 0.05 by the Holm procedure, independently of the primary result. All other outcomes are exploratory, reported as point estimates with 95% confidence intervals without multiplicity adjustment and interpreted as hypothesis-generating; postoperative complications are additionally analyzed with multivariable adjustment for extent of resection, surgical approach, and comorbidity, and a subgroup analysis by extent of resection (total versus distal gastrectomy) is prespecified as exploratory via a treatment-by-subgroup interaction. Following ICH E9(R1), the primary estimand is the between-arm difference in mean POD 5 nitrogen balance in the intention-to-treat population under a treatment-policy strategy: PN dose reduction or discontinuation is handled by using the observed POD 5 value and is not treated as missing. Genuine missing data (death before POD 5 or failed collection) are addressed by multiple imputation under missing-at-random as the primary approach, with complete-case analysis as sensitivity; because complication-related missingness may be non-random, a delta-adjusted (tipping-point) sensitivity analysis is performed.

**Other considerations.** No interim efficacy analysis is planned. The full statistical analysis plan, including detailed analysis specifications for each outcome, is finalised and dated before release of the coded treatment labels for the primary analysis. All analyses are conducted using R (R Foundation for Statistical Computing, Vienna, Austria).

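### The laboratory safety row of Table 4 compares the arms at POD −1, the protocol's own baseline, and names no use of that baseline at later visits

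*Protocol article*

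**What the plan says.** All references are to the protocol article.

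- **Table 4, Laboratory safety row.** The analytes are "Aspartate and alanine aminotransferase, blood urea nitrogen, serum creatinine, glucose, electrolytes", the timepoints "POD −1, POD 3, POD 5, 1, 3, 6, 12 months", and the analysis "Descriptive summary; between-group comparison at each timepoint". The row names no test, change score, baseline covariate or repeated-measures model.
- **Notes to Table 4.** "Two-sided α = 0.05 will be used throughout". Early prealbumin change is "defined as the change from the preoperative (POD −1) baseline to POD 5", so the protocol treats POD −1 as a baseline visit. Full specifications are referred to SAP v1.0, which is not available here.
- **Interventions, Stepwise PN delivery schedule.** The allocated product starts on the same day: "PN is initiated on the preoperative day (preoperative day −1; POD −1"). The scheduled proportions of the caloric target are "80% on POD −1, 100% on POD 1, 60% on POD 2 and POD 3, and 50% on POD 4 and POD 5". The article does not say whether the POD −1 blood sample comes before or after the start of that infusion.
- **Statistical analysis, secondary outcomes.** Apart from the primary and two key secondary endpoints: "All other outcomes are exploratory, reported as point estimates with 95% confidence intervals without multiplicity adjustment".

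**The concern.** A between-arm comparison of a value measured before treatment in a randomised trial has a known answer: any difference is due to chance. Listing it with the on-treatment comparisons, with no multiplicity adjustment, invites a reader to take a chance difference in, say, an aminotransferase or creatinine as a finding.

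At the later visits, a participant's own starting value usually explains part of the spread in the later value. If the comparison takes no account of it, the interval for a product effect on liver or kidney tests is wider than the collected data allow. The estimate also moves with whatever chance imbalance was present at the start. What is at stake is the clarity and precision of the exploratory safety tables, not the trial's main conclusion.

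**Working it through.** **Inputs from the protocol article**

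- Seven laboratory timepoints, of which POD −1 is the first (Table 4).
- Five named analytes (AST, ALT, blood urea nitrogen, creatinine, glucose) plus electrolytes, whose number is not given (Table 4).
- Two-sided α of 0.05 (notes to Table 4).
- 55 per arm (Sample size). This reproduces: a difference of 3 g/day with SD 5 g/day at 80% power gives 2 × (1.96 + 0.84)² × 5² ÷ 3² ≈ 43.6, so 44 per arm, and 44 ÷ (1 − 0.20) = 55.

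**Assumptions**

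- 3 to 6 electrolytes, so 8 to 11 analytes.
- Independent analytes. Related pairs such as AST and ALT will depart from this.
- A baseline-to-follow-up correlation r of 0.3, 0.5 or 0.7. The documents give no value.

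**Step 1. Comparing POD −1, if the blood precedes PN.**

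Comparisons in the row: 8 × 7 = 56 to 11 × 7 = 77, of which 8 to 11 fall at POD −1.

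Expected chance differences at p < 0.05: 8 × 0.05 = 0.40 to 11 × 0.05 = 0.55.

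Probability of at least one:

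- 8 analytes: 1 − 0.95⁸ = 0.34
- 11 analytes: 1 − 0.95¹¹ = 0.43

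The same figures apply if no p-values are printed but 95% confidence intervals are read for whether they exclude zero.

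**Step 2. Leaving baseline out at later visits.**

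In SD units, the standard error of an unadjusted difference is √(2/n); with n = 55 this is 0.191. Adjusting for baseline multiplies it by √(1 − r²). Power is shown for an assumed true difference of 0.5 SD, as Φ(0.5/SE − 1.96).

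| Assumed r | Adjusted variance ÷ unadjusted, 1 − r² | Unadjusted variance ÷ adjusted | Adjusted SE | Power |
|---|---|---|---|---|
| no adjustment | 1 | 1 | 0.191 | 74.6% |
| 0.3 | 0.91 | 1.10 | 0.182 | 78.5% |
| 0.5 | 0.75 | 1.33 | 0.165 | 85.7% |
| 0.7 | 0.51 | 1.96 | 0.136 | 95.7% |

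A simple change from baseline is not an equivalent substitute. Its standard error is √(2/n) × √(2(1 − r)), which at r = 0.3 is 0.226, worse than the unadjusted 0.191. At r = 0.5 it equals the unadjusted value.

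**Step 3. Whether POD −1 is a clean baseline.**

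The notes to Table 4 call POD −1 a preoperative baseline, which means before surgery. The delivery schedule starts the allocated product that same day at 80% of target. Both statements can hold, but together they do not show that the sample was taken before PN. Step 1 holds only if it was, and so does using POD −1 as the covariate.

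**The case against.** The strongest reply is that the row is short because the detail belongs in the SAP. Whether an exploratory laboratory comparison carries a baseline covariate is commonly settled there, and the row does not exclude one. This stands in part. A reader might infer that the trial discards its baseline values; the document does not say so, only that this row names no use of them. The reply does not cover the POD −1 comparison. The row lists that visit and prescribes a comparison at every listed visit, separately from the descriptive summary, so this is stated rather than omitted.

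A second reply is that no test is named and the outcomes are exploratory. That is fair, and the 34% to 43% is therefore conditional on testing, or on reading intervals as tests. The α statement in the table notes makes that reading reasonable.

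A third is that the POD −1 sample may be drawn after PN starts, in which case comparing the arms at that visit would be legitimate. This stands, and the fix has to depend on the answer.

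A reader might also link the point to the absence of a monitoring board. The link is weak. Day-to-day protection rests on the daily glucose, electrolyte, hepatic and renal monitoring described under Monitoring and dose modification, and on adverse event review. None of that depends on how the laboratory values are modelled.

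**Conclusion.** The point holds as a minor one. As written, Table 4 includes a between-arm comparison at the baseline visit. If the sample precedes PN, that comparison is uninformative and has about a 34% to 43% probability of producing at least one nominally significant difference, for 8 to 11 independent analytes. At later visits the cost is precision: variance 1.10 to 1.96 times the adjusted one for r from 0.3 to 0.7. The analyte count, the independence and every r are assumptions.

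Two stronger readings are tempting and not supported. One is that the later comparisons are biased or invalid. Under randomisation they are neither, and their intervals already allow for chance imbalance. The other is that the exclusion limits in Table 1 show a wide baseline spread. They are ceilings applied at screening and do not give the SD of the values at POD −1.

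The primary and key secondary results are not affected.

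**What to change.** In the Laboratory safety row of Table 4, and in the SAP where needed:

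1. Limit between-group comparisons to the post-baseline visits (POD 3, POD 5 and 1, 3, 6 and 12 months).
2. Summarise POD −1 by arm descriptively, with no between-arm comparison.
3. Compare each later value with the participant's pre-PN value as a covariate, and report the adjusted difference with its 95% confidence interval.
4. State whether POD −1 blood is drawn before the first PN infusion. If it is not, use the screening value as the covariate where that analyte was measured. The Table 1 limits imply screening values for AST, ALT, creatinine, sodium, potassium, calcium and magnesium. They list neither blood urea nitrogen nor glucose itself.

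The cost is a few lines of wording and a simple rule for participants without a baseline value. No new data are needed, and the trial is still recruiting with no between-group analysis reported.
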